### **Design and description of the study**

This is a prospective randomized 2-arm study (performed in 3 hospitals). Consecutive patients with at least 1 lesion suspicious of melanoma (following clinical and dermoscopy evaluation) will be enrolled. Patients will be randomized to the standard therapeutical care ("Clinical and dermoscopy evaluation only") or standard therapeutical care + RCM integration ("RCM evaluation + clinical and dermoscopy evaluation") following identification of a suspicious lesion during the standard therapeutical care.

The main objective is to evaluate the safety of the integration of RCM (diagnostic identification of melanomas) and cost-effectiveness in terms of the comparison of the number of excisions needed to identify 1 melanoma (including the follow-up period). A cost-utility model will be developed to quantify the impact of the proposed triage system on health care costs and diagnostic effectiveness. This model will be tested on the study population.

Patients will be selected consecutively among patients with suspected skin cancer.

Randomization will be allocated at a 1:1 ratio and patients will be allocated to the “RCM evaluation + clinical and dermoscopy evaluation” or “Clinical and dermoscopic evaluation only” following standard therapeutic care; patients allocated to “Clinical and dermoscopic evaluation only” will likely require immediate biopsy for diagnosis, whereas clinicians of patients allocated to the “RCM evaluation + clinical and dermoscopy evaluation” can decide based on RCM evaluation whether to excise the lesion or refer the patient to subsequent digital follow up. Lesions referred to follow-up will be monitored for at least 6 months, and excised if significant changes are observed on dermoscopy.

In detail, the therapeutic-diagnostic pathway for each study arm are as follows:

a) "RCM evaluation + clinical and dermoscopy evaluation": following routine therapeutic care (clinical-dermoscopic examinations) clinicians of patients with suspicious lesions (at least one major or minor clinical and / or dermoscopic criterion for malignancy, as per inclusion / exclusion criteria) will be able to evaluate the lesions with RCM. A clinical decision (removal or digital dermoscopic follow-up) will be made based on the RCM evaluation.

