b) "Clinical and dermoscopic evaluation only": following routine therapeutic care (clinical-dermoscopic examinations) clinicians of patients with suspicious lesions (at least one major or minor clinical and / or dermoscopic criterion for malignancy, as per inclusion / exclusion criteria), will make a clinical decision (removal or digital dermoscopic follow-up) without RCM evaluation.

Each participating center will be responsible for its own case history and clinical decisions. Each center will take care of the collection and storage of data. At interim analysis (18 months) collected data and preliminary results will be evaluated collectively and discussed. The investigators at the participating centers have high-level therapeutic-diagnostic pathways in place, as documented by the numerous publications produced by these centers, however, in case of significant discrepancies among the interim clinical performance data, or if requested by individual investigators, some cases may be evaluated independently by other investigators in order to verify diagnostic agreement. These cases may derive either from direct indications from the investigators or randomly selected from the collected cases.

Images will be anonymized and only essential clinical data (sex / age, any significant present or past pathologies) will be provided to the other evaluators.

The definition of the head / neck lesion subset is as follows:

1. Malignant macules with histological diagnosis of melanoma;
2. Benign macules with histological diagnosis of actinic keratoses, solar lentigos, lichen planus-like keratosis, seborrheic keratoses, freckles and junctional / compound / dermal nevi;
3. Benign macules not subjected to biopsy and with clear and defined parameters of clinical, dermoscopic and confocal microscopy benignity;

The main outcome will be the rate of malignant lesions identified within the "RCM evaluation + clinical and dermoscopy evaluation" compared to "Clinical and dermoscopic evaluation only" study arms.

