### **Statistical analysis**

Randomization: the "sample" function of STATA 13 (STATA Corp. College Station, Texas 2014) will be used weekly to predetermine the allocation of the subjects, in an alternating random manner, into the two study arms.

In the Coordinating Center, an estimated 800 patients will be enrolled (a total of 400 cases per study arm).

Outcomes include diagnostic safety of the RCM tool (measured by the number of excisions in relation to the number of melanomas diagnosed), a cost-benefit / efficacy calculation (based on an economic-drug model developed within the studio).

The estimated number of delayed cancer diagnosis within the "RCM evaluation + clinical and dermoscopy evaluation" study group is less than 1%.

Study power calculation: The expected percentage of melanomas identified in the "Clinical and dermoscopic evaluation only" group is 7.3% (Carli P, De Giorgi V, Nardini P, Seidenari S, Pellacani G, Peris K, Piccolo D, Rubegni P, Perotti R. *Skin Cancer Day in Italy: tumor detection rate and pattern of referral of open access clinics in an intermediate melanoma risk population. Eur J Dermatol* 2003; 13: 76-79) and for the "RCM evaluation + clinical and dermoscopy evaluation" group is 14% (Guitera P, Pellacani G, Longo C, Seidenari S,

As outlined in literature, approximately 22.4% of patients with "atypical" lesions are sent for treatment in highly experienced centers, equipped with digital dermoscopy (Alarcon I, Carrera C, Palou J, Alos L, Malveyh J, Puig S. *Impact of in vivo reflectance confocal microscopy on the number needed to treat melanoma in doubtful lesions. Br J Dermatol.* 2014; 170: 802-8) therefore, the enrolment of at least 2375 patients is required. Each collaborating center will enroll about 800 subjects.

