**Inclusion criteria:**

- 1) Adult patients (18-90 years) referred to the Dermatology departments of the collaborating centers.
- 2) Patients able to give consent to participate
- 3) Patients with at least 1 lesion with at least one major or minor clinical and / or dermoscopic criterion of suspicion of malignant tumor lesion (Friedman 1987; Argenziano 2002) identified during the clinical and dermoscopy evaluation.
- 4) Willingness to participate in the study and able to give written informed consent

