**Exclusion criteria:**

- 1) Patients <18 years old
- 2) Comorbid dermatological pathologies that can alter the visualization of the lesions in RCM, such as extensive hyperkeratotic skin diseases or widespread eczema.
- 3) Physiological, general pathological or psychiatric conditions that prevent the patient from being able to lie down for at least 10 minutes (time of RCM evaluation)
- 4) lesions with alterations (ulceration, crust, hyperkeratosis) which prevent RCM visualization.

Additionally, in a smaller population of patients classified at high risk of melanoma, will be evaluated with a total body examination with the RCM (VivaScope 3000) for each melanocytic skin lesion in addition to classic videomicroscopy. Suspected lesions in dermoscopy and / or RCM will be excised. Subsequently, the accuracy of excisions will be compared for both groups, and the benefit of the combined approach to the patient will be calculated. A population of about 300 patients at high risk of developing melanoma (> 100 nevi, > 4 atypical nevi) will be required. These tests will be performed in two of the collaborating outpatient clinics, performed by 2 interchangeable expert specialists (both will examine 50% of the population with dermoscopy and 50% with RCM). Coincident and

discordant data in case of equivocal injury will be compared. Any lesion showing features in dermoscopy and / or confocal that are suspicious of melanoma will be excised. In high-risk patients, any lesions that do not show clear benign features will be routinely monitored with digital videodermoscopy for at least six-months.

The main objective in this case is the quantification of detection of suspected and confirmed malignant lesions on histological examination after excision, with respect to the standard of care (clinical examination + videomicroscopy). The time required for the total-body examination will be measured and compared with a standard videomicroscopy to estimate the cost-benefit value of the procedure.

The previously described statistical tests (chi-square and Z-test) will be applied.

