### **Data collection**

Patients will be coded on the basis of a code generated for each patient enrolled which includes 2 letters (indicating city of enrollment) and 4 consecutive digits (in order of enrolment). In case of multiple lesions for a single patient, lesions will be assigned a letter (A, B, C etc). Essential clinical information for each patient will be collected on an EXCEL file (Gender, age, phototype, number of nevi, number of atypical nevi, family and / or personal history of melanoma, clinical signs of photodamage). For each lesion, the outcome decided during the visit (excision, follow-up) will be indicated. In the event of a lesion referred for follow-up, the subsequent Clinicians' decision (no further follow-up, further follow-up or excision) will be noted.

In the case of excision, upon histological referral, a coded diagnosis will be entered for all the major diagnostic categories. A different EXCEL file, stored on a separate hard-disk and not connected to an external internet network, will collect the code assigned to the patient, the patient's personal data, the date of the visit, any date on which the follow-up is planned / scheduled and personal contact information (telephone / email, etc.) useful for contacting the patient in case the patient does not present for the scheduled follow-up visit. The images coded as described above, without being able to recognize the patient, will be collected on a local Server, with exclusive access allowed by the investigators, through a personal password.

Image management: the images obtained will be coded on the basis of the code generated for each patient enrolled. The images will be stored on local systems (at each individual collaborating center).

Missing data management: any eventual loss of participation by patients' refusal to participate in the study and generated by the randomization process will be compensated the following week, to assure that the number of the patients within both study groups meet the planned dimensions. In case of patients' refusal for surgical intervention, the subject will remain in the study and be monitored over time with a digital follow-up (routine

clinical practice in the case of patients who refuse intervention for lesions without significant suspicion of malignancy), in order to identify lesion modifications, such as increased suspicion of malignancy, enabling a strong recommendation for lesion excision.

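### The lesion list is not closed before the arm is known, and two subsets admit benign lesions on RCM findings, so per-lesion rates can differ between arms without any RCM effect

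*Protocol*

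**What the plan says.** - **Timing.** Under Design and description of the study, patients are randomised "following identification of a suspicious lesion during the standard therapeutical care". Inclusion criterion 3 admits "Patients with at least 1 lesion with at least one major or minor clinical and / or dermoscopic criterion". One qualifying lesion therefore precedes allocation. No index lesion is named and no maximum is set.
- **Allocation.** Under Statistical analysis, a software function "will be used weekly to predetermine the allocation of the subjects, in an alternating random manner, into the two study arms".
- **Lesion registration.** Under Data collection: "In case of multiple lesions for a single patient, lesions will be assigned a letter (A, B, C etc". The record is then kept by lesion: "For each lesion, the outcome decided during the visit (excision, follow-up) will be indicated". No time point is given at which the list is complete.
- **Lesion-level exclusion.** Exclusion criterion 4 removes "lesions with alterations (ulceration, crust, hyperkeratosis) which prevent RCM visualization", again without saying whether this is judged before or after allocation.
- **Subsets.** The third category of the head/neck subset and the fourth of the non-melanocytic subset admit benign lesions without histology. They qualify on clinical, dermoscopic and confocal (RCM) signs of benignity.
- **Outcome.** After the head/neck definition the protocol states: "The main outcome will be the rate of malignant lesions identified within the" RCM arm compared with the control arm. Sensitivity, specificity, accuracy and odds ratios follow for both subsets.

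**The concern.** The clinician who codes lesions knows the arm, because RCM is either available or not. Registering a further doubtful lesion has different consequences in the two arms. With RCM it can be imaged and sent to digital follow-up. In the control arm the Design section expects that immediate biopsy will likely be needed. Lesions beyond the qualifying one can therefore enter the data at different rates for reasons unrelated to diagnostic performance.

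The subset definitions add a second route that does not depend on anyone's behaviour. Read literally, a control-arm lesion that is left in place cannot meet a criterion that includes confocal findings, because it has not been imaged. An identical lesion in the RCM arm can.

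What is at stake is any comparison whose denominator is lesions. Randomising patients 1:1 balances patients. It does not balance a set of lesions that is completed after the arm is known.

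**Working it through.** The protocol gives no number of lesions per patient, so there is no planned figure to reproduce here. The calculation only shows direction and scale.

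**Inputs**
- Malignant rate at entry: 7.3%, the control-arm melanoma percentage in the power calculation (Statistical analysis). It is stated there for subjects and is used here as a per-lesion rate, assuming one entry lesion per patient.
- Extra lesions per RCM patient: x = 0.1, 0.2 or 0.3 (assumption). All are benign and deferred.
- No RCM effect: entry lesions are handled identically in both arms, and all malignant ones are excised.
- Specificity is taken as the share of benign lesions not excised (assumption).

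**Route 1: extra lesions coded in the RCM arm**

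Malignant rate per lesion = 0.073/(1 + x).

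Specificity if every entry lesion is excised = x/(0.927 + x), against 0 in control. If instead 80% of entry lesions are excised (assumption), 0.2 benign lesions per patient are already left in place. Specificity is then (0.2 + x)/(0.927 + x), against 0.2/0.927 = 21.6% in control.

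| x | Malignant rate | Specificity, all entry lesions excised | Specificity, 80% excised |
|---|---|---|---|
| 0 (control) | 7.3% | 0% | 21.6% |
| 0.1 | 6.6% | 9.7% | 29.2% |
| 0.2 | 6.1% | 17.7% | 35.5% |
| 0.3 | 5.6% | 24.4% | 40.7% |

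If 2% of the extra lesions were malignant, the rates would be (0.073 + 0.02x)/(1 + x) = 6.8%, 6.4% and 6.1%.

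With 400 patients per arm (the coordinating centre's figure) and independent lesions, the chance of a nominally significant two-sided 5% difference in malignant rate is 6.6%, 11.2% and 18.0% for x = 0.1, 0.2 and 0.3 with no malignant extras. With 2% malignant extras it is 5.9%, 8.1% and 11.5%. Subset sizes are not given. A smaller subset would bring these chances closer to 5%.

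**Route 2: entry on RCM benignity, with no extra lesions at all**

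Let 80% of lesions be excised in both arms, and let every deferred RCM-arm lesion meet the benignity category. The RCM subset keeps 1 lesion per patient, so its malignant rate is 7.3%. The control subset keeps only the 0.8 with histology, so its rate is 0.073/0.8 = 9.1%. Specificity is 0.2/0.927 = 21.6% in the RCM arm. In control it is 0/0.727 = 0%. The arms behave identically and only the entry rule differs.

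**What does not move**

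Take 100 patients per arm with all entry lesions excised. Each arm has 7.3 malignant and 92.7 excised benign lesions, or 92.7/7.3 = 12.7 benign excisions per malignant lesion. Adding 10, 20 or 30 deferred lesions to the RCM arm changes neither number.

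**The case against.** **The steps are already ordered.** Qualifying lesions are found in the clinical and dermoscopic evaluation under the same criterion in both arms, and randomisation follows. This stands for the qualifying lesion. It does not cover further lesions, for which no time point is given.

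**The main endpoints are not touched.** The main objective in the Design section is safety and the number of excisions per melanoma. The number needed to excise uses excised lesions only. A reader might infer that extra deferred lesions could imitate much of the planned 30% reduction, since the excised share per lesion, 1/(1 + x), would fall by 9%, 17% or 23%. The documents do not support this. The aim concerns the reduction of unnecessary excisions, and no per-lesion excised share is named as an endpoint. In this scenario no excision is added or removed.

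**The malignant rate shifts against RCM.** The power calculation expects a rise from 7.3% to 14%, and the distortion lowers the RCM figure. This stands for that rate. Specificity shifts the other way.

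**The main-outcome sentence belongs to the head/neck text and names no denominator.** This also stands, so the point on that rate is limited to the subsets and holds only if the rate is taken per lesion.

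**The mechanism may be weak.** Control clinicians may also choose follow-up, and RCM takes at least 10 minutes, which limits casual imaging. Both are fair, and they are why the size is uncertain. Neither affects the second route, which follows from the subset definitions.

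**The analysis plan could settle it.** It can name the analysis unit. It cannot recreate a pre-allocation list that was not made at the visit.

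**Conclusion.** The point holds for measures with a per-lesion denominator: specificity, and the between-arm malignant-lesion rate in the head/neck and non-melanocytic subsets if computed per lesion. As written, the lesion set behind them can depend on the arm in two ways: an open lesion list, and entry on findings that only one arm can produce.

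Under the stated assumptions, 0.1 to 0.3 extra benign deferred lesions per RCM patient lower that arm's malignant rate from 7.3% to between 6.6% and 5.6%, against RCM. Apparent specificity rises from 0% to between 9.7% and 24.4%, or from 21.6% to between 29.2% and 40.7% if 80% of entry lesions are excised. The extra-lesion numbers and the 80% are assumptions. The documents show that this can happen, not that it will.

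Excision counts, the number needed to excise and the 30% aim are unaffected as long as the extra lesions are never excised. A reader should not conclude that the trial's headline excision result is open to this distortion. It is a modest defect of the lesion-level comparisons and is cheap to remove.

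**What to change.** 1. Under Data collection, state that every lesion meeting inclusion criterion 3 on clinical and dermoscopic grounds is listed and lettered before the patient's allocation is revealed. Apply exclusion criterion 4 at the same point, by the same visual judgement in both arms.
2. Restrict the between-arm lesion comparisons, including both subsets, to listed lesions. Define subset entry for unbiopsied benign lesions by information obtainable in both arms, such as clinical-dermoscopic findings and the digital follow-up already provided for. RCM findings can be recorded as a result but should not decide entry.
3. Record lesions added after allocation and report them separately by arm, with their number, decision and histology where available.
4. State the denominator (patients or lesions) for the malignant-lesion rate.

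The cost is one step moved ahead of allocation at the same visit, plus a few sentences of text. Patient care does not change. The downside is that lesions noticed later leave the main comparison. Reporting them separately keeps them visible and shows whether the arms differ in how many are added.

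### Losses tied to randomisation are made up the following week to fill both arms, under a weekly allocation scheme worded both as alternating and as random; this puts the randomised comparison at risk.

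*Protocol*

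**What the plan says.** Three parts of the Protocol bear on this.

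- **Recruitment and timing (Design and description of the study).** The trial enrols "Consecutive patients with at least 1 lesion suspicious of melanoma", and randomisation takes place "following identification of a suspicious lesion during the standard therapeutical care". On the ratio it says "Randomization will be allocated at a 1:1 ratio". The order of consent and disclosure of the arm is not stated. The Inclusion criteria require consent and willingness to take part, but do not settle that order.
- **Allocation (Statistical analysis, Randomization).** Stata's sample function "will be used weekly to predetermine the allocation of the subjects, in an alternating random manner, into the two study arms". The text does not say who holds the weekly list or whether recruiting clinicians can see it.
- **Refusals (Data collection, missing data management).** Loss through refusal to participate and "generated by the randomization process will be compensated the following week", the purpose being "to assure that the number of the patients within both study groups meet the planned dimensions". Refusal of surgery is treated differently: "the subject will remain in the study and be monitored over time with a digital follow-up".

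**The concern.** A loss that arises from the randomisation process, and that can leave a study group short, is most naturally a patient who was allocated and then declined. A refusal before allocation belongs to no arm. The rule replaces such patients, and nothing says that they stay counted in the arm to which they were allocated.

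Two things are at stake.

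- **Selection after allocation.** The arms lead to visibly different routes. The Design section expects immediate biopsy to be likely without RCM, whereas with RCM the clinician may choose digital follow-up. Willingness to accept a given route may depend on how worrying the lesion looks, and hence on the chance of melanoma. The outcomes are melanoma frequency and the number needed to excise (NNE), so selection of this kind acts on the endpoint itself.
- **Foreseeable allocation.** If a short arm is topped up the following week, that week departs from 1:1 in a direction that staff can work out, because they saw who refused. Alternation is deterministic and so cannot also be random. The clinicians who judge suspicion also manage the patients, and they cannot be masked to RCM.

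**Working it through.** The Protocol gives no refusal rate and no estimate of this bias, so there is no figure of its own to reproduce on this point. What follows is an illustration.

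**Inputs from the Protocol (Statistical analysis).** Melanoma rate with clinical and dermoscopic evaluation only: 7.3%. Rate assumed with RCM: 14%. Calculated number of subjects: 532, or 532/2 = 266 per arm. Planned enrolment: 532/0.224 = 2375, as stated, or about 1187 per arm. Coordinating Center: 400 per arm. Test: chi-square.

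**Assumptions.** The true rate is *p* = 7.3% in both arms (no effect). A share *r* refuses after allocation, in one arm only. Refusers have melanoma rate *q*. They are replaced by later patients who accept that arm.

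**Step 1: rate in the affected arm.** After replacement the arm consists of acceptors only, so its rate is (*p* − *r* × *q*)/(1 − *r*), however many replacements are recruited. At *r* = 10%:

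- no melanomas among refusers: 7.3/0.90 = 8.1%
- twice the risk (14.6%): (7.3 − 1.46)/0.90 = 6.5%
- a rate of 20%: (7.3 − 2.0)/0.90 = 5.9%

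The same formula over a range:

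| Refusal in one arm | Refusers: none | Refusers: 14.6% | Refusers: 20% |
|---|---|---|---|
| 5% | 7.7% | 6.9% | 6.6% |
| 10% | 8.1% | 6.5% | 5.9% |
| 15% | 8.6% | 6.0% | 5.1% |
| 20% | 9.1% | 5.5% | 4.1% |

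If refusal is unrelated to risk (*q* = *p*), the rate stays at 7.3%.

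**Step 2: effect on the test.** Let *pa* be the rate from step 1 and δ = (*p* − *pa*)/√[*p*(1 − *p*)/*n* + *pa*(1 − *pa*)/*n*]. A nominal two-sided 5% test then rejects with probability 1 − Φ(1.96 − δ) + Φ(−1.96 − δ). For *n* = 1187 and *pa* = 6.49%, δ = 0.0081/0.0104 = 0.78, and the rejection probability is 0.119 + 0.003 = 12.2%. The ranges below run over refusers with no melanomas and refusers with twice the risk:

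| Refusal in one arm | 266 per arm | 400 per arm | 1187 per arm |
|---|---|---|---|
| 5% | 5.3% | 5.5% | 6.5% |
| 10% | 6.4–6.6% | 7.2–7.4% | 11.5–12.2% |
| 20% | 12–14% | 16–18% | 37–44% |

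The error grows with enrolment because the shift stays fixed while the standard error shrinks.

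**Step 3: foreseeability.** For a 1:1 list of known length 2*m*, a person who tracks past allocations guesses correctly an expected share [*m* + (4^*m*/C(2*m*, *m*) − 1)/2]/(2*m*). For a list of 10: (5 + (1024/252 − 1)/2)/10 = 65%. For a list of 20: 62%. Simple randomisation gives 50% and strict alternation 100%. The list lengths are assumptions.

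**The case against.** The strongest reply is that the damaging reading is only one of several.

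- **The refusal sentence is ambiguous.** It may join two harmless things: refusal before enrolment, and chance imbalance in arm sizes. The consent criteria fit that reading. This stands as a real alternative, but the aim of filling both groups fits the other reading better, and the text does not exclude it.
- **How losses are compensated is not stated.** Recruiting more patients through the same 1:1 process would also satisfy the sentence. This stands; an arm-specific top-up is plausible, not explicit.
- **Strict alternation.** A reader might infer that patients are simply alternated. The documents do not support that: the phrase also says random, a random sampling function is named, and the Design section specifies 1:1 randomisation. What remains is self-contradictory wording.
- **Lack of concealment.** A reader might infer that clinicians see the list. The Protocol is silent, and a list drawn up in advance can be concealed.
- **Refusal of surgery is covered.** Those patients stay in the study, so the refusal most closely tied to excision triggers no replacement. This stands and narrows the point.
- **Motive.** RCM adds an examination of about 10 minutes (Exclusion criteria), and removal remains available in that arm, so a patient who wants excision has limited reason to leave. This weakens any particular scenario, but it does not show that refusal would be unrelated to risk.

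Analysis-set rules may sit in a statistical analysis plan that is not shown. The replacement rule itself, however, is fixed in the Protocol.

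**Conclusion.** The concern holds as a risk written into the plan. If patients decline after learning their arm, the compensation rule makes the analysed arms differ from the randomised ones, and further recruitment does not cure this. If the top-up is arm-specific, the next week's allocations become partly foreseeable. The allocation wording contradicts itself in any case.

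Size and direction are undetermined. At an assumed 10% refusal in one arm, the shift runs from +0.8 points (8.1%) to −1.4 points (5.9%) around 7.3%. Against the planned difference of 14 − 7.3 = 6.7 points, that is about 12% to 21% of the effect. Less refusal, refusal unrelated to risk, or similar refusal in both arms would shrink or remove it. The effect on NNE cannot be computed, because it also depends on the refusers' benign excisions.

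A reader might infer that the arms are not randomly formed, or that melanomas in the RCM arm will be understated. Neither is shown: the first rests on silence about concealment, the second on one choice of refuser risk.

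**What to change.** 1. State that consent is obtained before the allocation is revealed.
2. Delete the word alternating, and allocate each patient from a concealed random list. Say who holds it.
3. Delete the weekly compensation rule. If recruitment falls short, continue the same 1:1 list for both arms.
4. Count every randomised patient in the allocated arm, and report refusals after allocation by arm. Use their outcome data where consent allows; some who decline may supply none.

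Varying block sizes and stratification by centre would be good practice, but this point does not depend on them.

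The cost is small: a shared list, revised wording, and arm sizes that may differ slightly. The rule for patients who refuse surgery needs no change here. The changes should be in place before recruitment, because no analysis reliably recovers randomised patients who were replaced.
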